### **Participant timeline**

Enrollment and data collection started in November 2022. The recruitment will continue until the target population (78 nurses) is enrolled, which is expected to be ended in June 2023. And afterward, the data analysis will be implemented for publications.

### **Sample size**

The aim of the cluster RCT is to improve the adherence to delirium intervention of ICU nurses by using the *AI-AntiDelirium* compared to the PADIS guideline. We expect that adherence to delirium intervention in the *AI-Antidelirium* group is 80% and PADIS guideline group is 50%, suggesting that *AI-Antidelirium* has clinical significance in improving the adherence to delirium intervention of ICU nurses. Sample size calculations showed that 12 nurses in each cluster will provide 80% power and a two-sided significance level ( $\alpha$ ) of 0.05, with an intracluster (within-unit) correlation of 0.002. In addition, taking into account possible dropout rate of 10%, we plan to enroll 13 nurses in each ICU, the final sample size is 78 (13\*6) nurses.

### **Recruitment**

All recruitment will carry out by trained research staffs who will not involve in the intervention and blind to the nurses' group assignments. Researchers will screen

nurses daily base on the inclusion and exclusion criteria. Written informed consent will be obtained from all eligible nurses. To retain more nurses, research staffs will explain the benefit for nurses if this study successfully implement.

### **Randomisation**

The risk of between-group contamination is reduced by cluster randomisation, ICUs will be randomised 1:1 to receive either *AI-AntiDelirium* care or PADIS guideline. We plan to recruit 6 ICUs in two hospitals, and matching the types of ICU (considering the different types of ICU nursing process, workload and patients illness severity and other factors which will affect the nurses' adherence). The allocation sequence is based on computer-generated random numbers, which is performed by a statistician who is independent of data analyses and not involved in data collection. In order to ensure the allocation concealment, the statistician will inform the each ICUs' allocation code to the study coordinator. And then, the study coordinator will inform the ICU nurses about which group they are allocated. All eligible nurses are recruited until the sample size is enough.

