## Participants

Registered Nurses (RN) who worked in included ICUs were all recruited. Nurses were eligible for the study if they (1) had a minimum of 1 year experience in intensive care; (2) worked full-time in the unit; and (3) consented to participate in this study. Nurses who were on study programs outside the hospitals or on leave for various reasons during the study period were excluded.

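### Nurses who join after their ICU's arm has been disclosed consent and give baseline data knowing it; the Randomisation, Participant timeline and Recruitment sections need reconciling with Table 1, and the leave exclusion needs a date

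*Protocol*

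**What the plan says.** **Order of disclosure and entry.** In the Randomisation section, an independent statistician passes each ICU's allocation to the study coordinator, and then "the study coordinator will inform the ICU nurses about which group they are allocated". The next sentence reads "All eligible nurses are recruited until the sample size is enough".

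**Rolling entry.** Participant timeline states "Enrollment and data collection started in November 2022" and "The recruitment will continue until the target population (78 nurses) is enrolled", with the end expected in June 2023. The Recruitment section has staff screen nurses every day.

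**The other order.** Table 1 marks eligibility screening and consent under Recruitment. It lists allocation lower down, marked in the same column as the baseline items and above the interventions. The Data collection section puts consent first, then baseline characteristics (including cognitive load and knowledge), then the daily measures. It requires consent before participation but does not say before allocation or before disclosure.

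**Who is eligible.** Participants says "Registered Nurses (RN) who worked in included ICUs were all recruited". One criterion is that the nurse "consented to participate in this study". It also says "Nurses who were on study programs outside the hospitals or on leave for various reasons during the study period were excluded". Sample size plans 13 nurses per ICU, 78 in all.

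**Blinding and analysis.** Recruiters and outcome assessors are to be blind, and the Blinding section accepts that nurses cannot be. Statistical methods calls for intention-to-treat with multiple imputation.

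**The concern.** Randomising ICUs balances units, within the limits of six of them. It protects the comparison of individual nurses only if nobody enters on the basis of the unit's arm. Once a unit knows its arm, a nurse who likes the idea of the tool can choose to join an *AI-AntiDelirium* unit and a reluctant one can decline, with no matching pressure in the guideline units. The enrolled nurses could then differ between arms in motivation, and adherence, the primary outcome, is likely to depend on motivation.

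The baseline data are exposed in the same way. Knowledge is one of the planned adjustment covariates and cognitive load is a secondary outcome with a baseline value. If either is recorded after disclosure, it may already reflect the arm, and adjusting for it may not undo the selection.

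The leave exclusion raises a separate question: whether absence that begins after allocation can take an enrolled nurse out of the analysis.

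**Working it through.** **1. The plan's own figure.** The inputs from Sample size are 80% versus 50% adherence, two-sided 5% level, 80% power, within-unit correlation 0.002, and 12 nurses per ICU in six ICUs (36 per arm).

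- Unpooled formula: (1.960 + 0.842)² × (0.5×0.5 + 0.8×0.2) / 0.30² = 35.8 per arm.
- Design effect: 1 + 11×0.002 = 1.022, giving 36.5 per arm, or 12.2 per ICU.
- Power at 36 per arm is 79.4%, so 12 per ICU is reproduced. Allowing for dropout, 12/0.9 = 13.3 per ICU; the plan uses 13.

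This point disputes none of these figures. It concerns who the 78 nurses are.

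**2. The two orders side by side.**

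- Randomisation: allocate ICU, tell its nurses, recruit to target.
- Participant timeline and Recruitment: enrolment and data collection begin together, screening is daily, and entry stays open until 78 are reached.
- Table 1 and Data collection: screen and consent, baseline, allocation, interventions, daily measures.

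The Table 1 order could hold for every nurse only if entry in each unit closed before that unit was told its arm. No section says so, and an enrolment window of about seven months running alongside data collection makes it unlikely.

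**3. What a late joiner knows.** Allocation is by ICU, so a nurse who consents after disclosure in that unit takes a known arm. Consent is an eligibility criterion and the nurse's own decision. Blind recruiters remove the recruiter's influence but not the nurse's.

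**4. The leave rule.** Its wording covers absence at any time in the study and does not limit the rule to absence known at screening. On the narrow reading (judged at screening) it is an ordinary eligibility rule. On the wide reading (applied to enrolled nurses) it drops randomised participants for events after allocation, which intention-to-treat does not allow. The 10% dropout allowance and multiple imputation suggest such nurses should stay in, but the text does not settle it.

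**5. Size.** The documents do not give the number of nurses who consented after disclosure, the number excluded for leave, or any difference in their adherence. For illustration only, assume that a share q of one arm is selected in this way and that their adherence differs by d from that of the nurses they displace. The arm mean then shifts by q × d:

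- q = 10%, d = 10 points: 0.10 × 10 = 1 point
- q = 20%, d = 20 points: 0.20 × 20 = 4 points
- q = 30%, d = 30 points: 0.30 × 30 = 9 points

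The planned difference is 80% − 50% = 30 points.

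**The case against.** The strongest reply is Table 1. It places consent before allocation, and Data collection agrees, so the protocol can be read as already intending the right order. That stands in part: it rules out saying that all nurses were recruited after disclosure. It does not remove the problem for nurses joining a unit already told its arm, nor the conflict with the Randomisation section.

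Several stronger inferences are tempting and are not supported:

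- *Late recruitment breaches intention-to-treat.* It does not. That principle governs how enrolled participants are analysed; entry after disclosure is recruitment bias.
- *Enrolled nurses are removed when they take leave.* No section says this. The rule sits among the eligibility criteria, and Table 1 marks eligibility screening only at recruitment.
- *The first 13 volunteers in each ICU are taken.* The 13 is a planned number. How nurses are chosen if more are eligible is not stated.
- *Thirteen is a minority of each unit's staff.* The bed counts give (42 + 46)/6 = 14.7 beds per ICU, but turning beds into nurses needs a staffing ratio that the protocol does not give. The relevant pool is also narrower: full-time nurses with at least a year of ICU experience.

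It is also fair to say that even the largest illustrative shift is well below the planned 30 points. The bias matters more for the estimate itself, or if the true effect is smaller.

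**Conclusion.** The point holds in a limited form. The protocol gives two incompatible orders for disclosure and consent. Under the order in Randomisation, and for any later joiner under the rolling entry described elsewhere, nurses consent and provide baseline data knowing their arm. This is a recruitment-bias risk that blind recruiters do not remove. The leave exclusion is loosely worded, and it conflicts with intention-to-treat only if applied to nurses already enrolled.

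How many nurses are affected, and by how much, cannot be computed from the documents. The 1 to 9 points rest wholly on assumed shares and differences. A separate analysis plan could define the analysis set, but it could not undo selective entry, so the order of steps belongs in the protocol.

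**What to change.** Reconcile Randomisation, Participant timeline and Recruitment with Table 1, and state that:

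- in all six ICUs the list of eligible nurses is closed, and consent and baseline measures (including cognitive load and knowledge) are obtained, before any allocation is disclosed or arm-specific training starts;
- every consenting nurse is enrolled or, if more than 13 in an ICU consent, 13 are drawn at random;
- the leave and outside-study exclusion applies only to absences known when the list closes;
- every enrolled nurse is analysed in the allocated arm, with later absence handled as missing data.

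Enrolment had already begun in November 2022, so the order cannot be reversed for nurses who entered after disclosure. Record the consent date and the unit's disclosure date for each nurse, report how many joined afterwards by arm, and add a sensitivity analysis restricted to nurses who consented before disclosure.

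The cost is small: wording, the order of steps, two dates per nurse and one further analysis. The real downside is an earlier cut-off for new staff.

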### **Blinding**

Investigators who will enroll participants are are not made aware of the randomisation list and patients are kept unaware of their assignment. But the nurses who implement strategies are not be possible to blind the allocation due to the nature of the intervention. Baseline data and endpoints measures will be collected by data collectors or outcome assessors who have no role in the intervention and blind to the allocations.

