**Summary**

High cognitive load of nurses is a common problem in intensive care unit, which is associated with nurses' poor performance of activities, as well as related to poor patient outcomes. It remains unclear whether Artificial Intelligence Assisted Prevention and Management for **Delirium** (*AI-AntiDelirium*) results in reduction of cognitive load and enhances adherence to delirium intervention in ICU nurses. We aim to assess the effectiveness of *AI-AntiDelirium* on cognitive load and adherence to delirium interventions of ICU nurses and the impact of ICU delirium. This is a multicentre, prospective, cluster randomised controlled clinical trial comparing the impact of *AI-AntiDelirium* and PADIS guideline for ICU nurses. A total of six ICUs in two hospital will be randomised in a 1:1 ratio to receive either *AI-AntiDelirium* (intervention group) or PADIS guideline (control group), with target sample size of 78 ICU nurses. The primary endpoint will be the adherence to delirium interventions. The secondary endpoints will be the cognitive load which measured by an instrument for measuring different types of cognitive load (MDT-CL). The endpoints of patients included incidence and duration of ICU delirium, length of ICU and in-hospital stay, ICU and in-hospital mortality. Outcome assessments will be conducted by investigators who blind to group assignment. The repeated measures analysis of variance (RMANOVA) will be performed to detect the difference in adherence and cognitive load between groups. Generalized estimation equation will be performed to

test the difference in patient outcomes.

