g. **Implement individual, risk factors targeting interventions:** click the button of “nursing checklist” → the *AI-AntiDelirium* will automatically automatically display the specific execution time of each intervention basing on the results of nursing care plan → the nurse implements individual interventions during the whole shift and records reasons why the patient do not receive these interventions → the nurse clicks on the measure after implements it → the *AI-AntiDelirium* automatically record the nurse's name and the time of execution.

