### **Outcomes**

Endpoint assessment will implement by trained research staffs who will not involve in the clinical nursing care of patients.

**The primary outcome is adherence to the intervention, which** is defined as the adherence of nurses to implement ICU delirium and risk factors assessment, delirium prevention and management interventions every day. The reasons for non-adherence will record daily by the intervention staff.

- a. Adherence to ICU delirium assessment was calculated by dividing the number of actions to number of theoretical assessment. The theoretical ICU delirium assessment for each nurse per day was defined as twice daily multiply the number of patients cared by the nurse.
- b. Adherence to ICU delirium risk factors assessment was calculated by dividing the number of actions to number of theoretical risk factors assessment. The theoretical risk factors assessment for each nurse per day was defined as once daily multiply the number of patients cared by the nurse.
- c. Adherence to ICU delirium prevention or management intervention was calculated by dividing the number of actions to number of theoretical interventions implementation

**Secondary endpoints** will include cognitive load of nurses, **which** defined as the total amount of limited cognitive resources that a person is occupied during a cognitive task. Cognitive load was assessed by means of an instrument for measuring

different types of cognitive load (MDT-CL) with **ten-item**, which had been successfully used to distinguish different types of cognitive load. Each item score from 0 to 10, the higher of the score, the higher of the cognitive load. Cronbach's  $\alpha$  of Chinese version MDT-CL was 0.818, cronbach's  $\alpha$  values in measurement of intrinsic CL (Items 1, 2, and 3) was 0.879; cronbach's  $\alpha$  values in measurement of extraneous CL (Items 4, 5, and 6) was 0.878; cronbach's  $\alpha$  values in measurement of germane CL (Items 7, 8, 9, and 10) was 0.946.

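### Blinded endpoint assessment is claimed, but the design does not deliver it for adherence (primary) or cognitive load (secondary)

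*Protocol*

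**What the plan says.** Three places in the protocol present endpoint assessment as blind or independent of care:

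- Summary: "Outcome assessments will be conducted by investigators who blind to group assignment".
- Outcomes: "Endpoint assessment will implement by trained research staffs who will not involve in the clinical nursing care of patients".
- Blinding: "endpoints measures will be collected by data collectors or outcome assessors who have no role in the intervention and blind to the allocations".

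Strengths and Limitation then lists data collectors who do not know the allocation as an example of rigorous method.

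The protocol is open about the nurses. Blinding states that "the nurses who implement strategies are not be possible to blind the allocation due to the nature of the intervention", and Randomisation that "the study coordinator will inform the ICU nurses about which group they are allocated".

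On how the data arise, Intervention Groups, step g, says that "the nurse clicks on the measure after implements it", after which the app stores the nurse's name and the time. Under Control group, the nurse scores the delirium tool by hand, fills in the risk-factor form and enters interventions in the nursing care records. Outcomes adds: "The reasons for non-adherence will record daily by the intervention staff". Cognitive load is measured with the ten-item MDT-CL, each item scored 0 to 10. Data collection has it recorded, like adherence, at the end of each shift.

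**The concern.** Blinded assessment protects a comparison only if the person whose judgement or action produces the value does not know the arm. If an unblinded nurse produces the value and a blinded person gathers it, the gathering is blind and the measurement is not.

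This touches the primary endpoint and the nurse-level secondary endpoint. Cognitive load is subjective and open to expectation. Adherence is a count of recorded actions, and the two arms record actions by different means, so a difference in recording can look like a difference in care. If the blinding statement stands, the report could cite a protection that these two results do not have.

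**Working it through.** **Step 1. Who produces each value?**

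| Endpoint | App arm | Control arm | Knows the arm? |
|---|---|---|---|
| Adherence: delirium assessment | nurse completes items in the app | nurse scores and records by hand | yes |
| Adherence: risk-factor assessment | nurse completes list in the app | nurse fills in the form | yes |
| Adherence: interventions | nurse's click after each measure | nurse's entry in care records | yes |
| Cognitive load, 10 items | nurse (inferred) | nurse (inferred) | yes |
| Mortality, length of stay | not rated by nurses | not rated by nurses | not applicable |

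Sources: Intervention Groups steps d, e and g; Control group steps a to c; Outcomes; Summary. The last column follows from Randomisation and Blinding.

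**Step 2. What is inferred?**

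- Outcomes does not say that the MDT-CL is self-rated. It defines the construct as a person's own occupied mental resources and describes no observer, so self-report is the natural reading.
- Outcomes defines adherence as actions divided by theoretical actions without naming the source of the count. Data management mentions printed, precoded forms. The nurse-made records are the only ones described, and an app log and a care-record entry look different, so a collector using either would see the arm.

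**Step 3. Is the collectors' independence stated consistently?** Blinding says they have no role in the intervention. Outcomes gives the daily recording of non-adherence reasons to intervention staff. That term is undefined and the reasons are not an endpoint, but the two lines do not fit together.

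**Step 4. How much could it matter?** The documents give no bias figure, so this is an illustration on the protocol's own planning model.

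Reproducing the stated sample size (Sample size: 80% vs 50%, two-sided 0.05, power 80%, intracluster correlation 0.002, 12 nurses per ICU, three ICUs per arm):

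- n = (1.960 + 0.842)² × (0.80×0.20 + 0.50×0.50) / 0.30² = 7.849 × 0.41 / 0.09 ≈ 35.8 per arm
- design effect = 1 + (12 − 1) × 0.002 = 1.022
- 35.8 × 1.022 ≈ 36.5, so 37 against the stated 3 × 12 = 36. This reproduces the plan to within one nurse per arm.

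Now assume no true effect, both arms at 50%, with app-arm recording inflated by b. The effective n is 36 / 1.022 = 35.2 per arm, and

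P(significant in favour of the app) = Φ[(b − 1.96 × SE₀) / SE₁],

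where SE₀ is the pooled and SE₁ the unpooled standard error. For b = 0.10: SE₀ = √(2×0.55×0.45/35.2) ≈ 0.119, SE₁ = √((0.60×0.40 + 0.50×0.50)/35.2) ≈ 0.118, and Φ[(0.10 − 0.232)/0.118] ≈ 0.13.

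| Assumed inflation b | Chance of a significant result for the app |
|---|---|
| 0 | 2.5% (nominal, this direction) |
| 5 points | about 6% |
| 10 points | about 13% |
| 15 points | about 24% |
| 20 points | about 40% |

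The expected false difference is b whatever the number of nurses, so a larger trial would not remove it.

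**The case against.** The strongest reply is that the protocol says plainly that nurses cannot be blinded, so nothing is hidden and the fault is loose wording. That stands as to intent: unblinded nurses are unavoidable here and are not the defect. The defect is the separate claim that endpoint assessment is blind.

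Five stronger readings are tempting, and the documents do not support them:

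- A reader might infer that the blinding statement is empty altogether. It also covers enrolling staff and patients, Statistical methods adds a blinded analyst, and mortality and length of stay are not rated by nurses. None of that is refuted.
- A reader might take the app's click log to be the stated source of adherence. The protocol describes the click as a workflow step and does not name a source.
- A reader might see the retention message ("research staffs will explain the benefit for nurses if this study successfully implement") as a driver of bias towards the app. It comes from recruiters blind to allocation, is not limited to one arm, and its content is not given; success may mean only that the study is completed. It is at most a minor supporting point.
- A reader might want to put a number on the shift in cognitive load. The documents give no basis for one: they state no expected shift and no single total as the endpoint, and they split the items into three types of load, of which Strengths and Limitation says the app aims to reduce the extraneous type.
- A reader might propose trusting a cognitive-load difference only when adherence agrees. Both endpoints come from the same unblinded nurses, so agreement between them is no independent check.

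**Conclusion.** The claim of blinded endpoint assessment is wrong as written for adherence and cognitive load, and the point is limited to those two endpoints. It reaches all three adherence components and all ten MDT-CL items.

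It rests on two readings that the protocol leaves open: that nurses score the MDT-CL themselves, and that the adherence count draws on the records described. The first is close to forced by the construct. If the second is wrong because collectors observe care directly, they would still see which arm the ICU is in.

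The size of any bias is unknown. The 6% to 40% range in the working depends on an assumed inflation of 5 to 20 points, an assumed direction, and the planning model's treatment of adherence as a simple proportion of nurses. It shows why the protection matters and does not predict what will happen.

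**What to change.** 1. **Summary, Blinding, and Strengths and Limitation.** State that cognitive load is an unblinded self-report by nurses, and that adherence rests on nurse-made records whose format reveals the arm. Do not cite blinded assessment as a protection for these two endpoints. If the adherence count has another source, name it.
2. **Keep** the blinding statements for enrolling staff, patients, the analyst, and outcomes that nurses do not rate, such as mortality and length of stay.
3. **Outcomes and Blinding.** Reconcile the line that gives non-adherence reasons to intervention staff with the line that collectors have no role in the intervention.
4. **Recruitment (minor).** Replace the message about benefit with one neutral script for all ICUs: two ways of organising delirium care are compared, and it is not known which is better.

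The cost is wording, a less favourable blinding statement and one fewer retention message. Participant timeline has enrolment starting in November 2022, so the script can reach only nurses not yet recruited. The corrected blinding statement can still be made at any time before reporting.
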